## Abstract

**Background:**

In the UK, 1–2% of infants are born very preterm (<32 weeks of gestation) or have very low birth weight (<1500 g). Very preterm infants are initially unable to be fed nutritional volumes of milk and therefore require intravenous nutrition. Milk feeding strategies influence several long and short term health outcomes including growth, survival, infection (associated with intravenous nutrition) and necrotising enterocolitis (NEC); with both infection and NEC being key predictive factors of long term disability. Currently there is no consistent strategy for feeding preterm infants across the UK. The SIFT trial will test two speeds of increasing milk feeds with the primary aim of determining effects on survival without moderate or severe neurodevelopmental disability at 24 months of age, corrected for prematurity. The trial will also examine many secondary outcomes including infection, NEC, time taken to reach full feeds and growth.

**Methods/design:**

Two thousand eight hundred very preterm or very low birth weight infants will be recruited from approximately 30 hospitals across the UK to a randomised controlled trial. Infants with severe congenital anomaly or no realistic chance of survival will be excluded. Infants will be randomly allocated to either a faster (30 ml/kg/day) or slower (18 ml/kg/day) rate of increase in milk feeds. Data will be collected during the neonatal hospital stay on weight, infection rates, episodes of NEC, length of stay and time to reach full milk feeds. Long term health outcomes comprising vision, hearing, motor and cognitive impairment will be assessed at 24 months of age (corrected for prematurity) using a parent report questionnaire.

**Discussion:**

Extensive searches have found no active or proposed studies investigating the rate of increasing milk feeds. The results of this trial will have importance for optimising incremental milk feeding for very preterm and/or very low birth weight infants. No additional resources will be required to implement an optimal feeding strategy, and therefore if successful, the trial results could rapidly be adopted across the NHS at low cost.

**Trial registration:**

ISRCTN Registry; ISRCTN76463425 on 5 March, 2013.

## Background

### Outcomes affected by feeding strategies

In the UK, 1–2% of newborn infants are very preterm or have very low birth weight. Preterm birth is the major risk factor for infant mortality, with 73% of neonatal deaths in the UK occurring in infants born before 37 completed weeks of gestation [1]. As survival, especially of very preterm infants, has increased in recent years [2], the high prevalence of morbidity associated with preterm birth means that the assessment of long-term outcomes has become increasingly important [3].

Short and long-term outcomes for preterm infants are affected by strategies that reduce infection rates, lower NEC rates, promote adequate growth, and maintain access to tertiary level facilities. Optimising feeding strategies affects all of these outcomes. Benefits are therefore likely to arise both from the individual and combined effects of identifying the optimum feeding strategy, as the rates of such complications in very preterm infants are high. NEC severe enough to cause death or require surgery affects approximately 7.5% of infants born before 29 weeks gestation, and is the cause of death in 11% of the deaths of infants born before 32 weeks [4]. Late-onset infection affects around 25% of very preterm infants and is responsible for 10% of deaths in the same population. Long-term data following late onset infection or NEC suggest these conditions almost double the risk of poor neurodevelopmental outcome [5].

### Nutritional support of preterm infants and speed of increasing milk feeds

Every year in the UK around 8000 infants are born so preterm that they cannot initially be fed milk and therefore require intravenous nutrition. Milk feeding is gradually increased as the immature gut begins to tolerate milk and intravenous nutrition is correspondingly reduced, but there are few data determining how quickly this is best achieved [6].

One of the most serious complications of intravenous feeding is late-onset sepsis, which occurs in 27% of infants born weighing less than 1500 g at birth or under 29 weeks’ gestation [6]. Late-onset sepsis is known to cause poor long-term cognitive outcomes, liver damage and also sudden death from cardiac problems resulting from misplaced catheters [7–9]. One of the most common late-onset infections is ‘catheter-related bloodstream infection’; the risk of bloodstream infection being directly related to the time the catheter is indwelling in the bloodstream [10–12].

The more rapid advancement of enteral feeds described in this study will, in principle, reduce exposure to intravenous nutrition by causing infants to reach full milk feeds (tolerating 150 ml/kg/day for 3 consecutive days) about 4 days earlier than the slower advancement. Reducing exposure by this amount could reduce the number of infections by between 5 and 15 cases per 250 infants, which is an absolute risk reduction of 4%. This is possibly an underestimate of the reduction as infection risk increases with the length of time a catheter is in place [13, 14].

However, faster increases in milk feed volumes may increase the likelihood of NEC which, as well as being potentially fatal, may provoke intolerance of feeds or gut dysfunction that could result in longer times to achieve full feeds rather than shorter. Survivors of NEC also have significantly worse long-term outcomes across multiple developmental domains than those unaffected [5, 15].

Therefore, while emerging data suggest better health outcomes may be achieved with faster feeding increments, there are possible disadvantages and a randomised controlled trial is required to support a change in clinical practice [6].

### Trial objectives

The primary objective of the trial is to compare the effects of two speeds of increasing milk feeds on survival without moderate or severe disability at 24 months of age (corrected for prematurity). The secondary objectives are to assess the impact of the two speeds of increasing milk feeds on the incidence of sepsis and NEC, and other outcomes collected before hospital discharge.

## Methods/design

The trial is a multi-centre randomised controlled group trial (RCT) to assess whether the speed of increasing milk feed volumes (faster increase [30 ml/kg/day] versus slower increase [18 ml/kg/day]) in very preterm (<32 weeks) or very low birth weight infants (<1500 g) infants has any effect on survival without moderate or severe disability at 24 months corrected age.

Two thousand eight hundred infants from approximately 30 neonatal units will be recruited within the UK and Ireland over 3 years.

### Inclusion criteria

Gestational age at birth is <32 completed weeks, or birth weight <1500 gReceiving ≤30 ml/kg/day of milk at randomisationWritten informed parental consent is obtained

### Exclusion criteria

Severe congenital anomalyIn the opinion of the treating clinician, have no realistic chance of survivalUnlikely to be traceable for follow-up at 24 months of age (for example, infants of non-UK residents)

### Primary outcome

The primary outcome will be the proportion of infants surviving without moderate or severe neurodevelopmental disability at 24 months of age corrected for prematurity. This composite outcome will be determined by confirming that the child is alive or dead using records held and maintained by The Health and Social Care Information Centre and other central UK NHS bodies. For live infants, a parent report questionnaire will be used to assess sensory and gross motor impairment and standardised measures to assess cognitive function in order to identify children with:Moderate/severe visual impairment (reduced vision uncorrected with aids; or blind in one eye with good vision in the contralateral eye; or blind/perceives light only)Moderate/severe hearing impairment (hearing loss corrected with aids; or some hearing loss but not corrected by aids; or deaf)Moderate/severe gross motor impairment (unable to walk or sit independently)Moderate/severe cognitive impairment assessed using the Parent Report of Children’s Abilities–Revised (PARCA–R), a parent report measure of non-verbal cognitive and language development. Total PARCA–R scores <44 will be used to identify children with moderate/severe cognitive impairment [16]. This questionnaire has been shown to have at least 80% sensitivity and 80% specificity for identifying children with scores < −2SD on a Gold Standard development test [16, 17]

A child who has any one or more of these impairments will be classified with a moderate/severe disability. Definitions for motor and sensory impairments described above are as defined in the report published by British Association of Perinatal Medicine (BAPM) in 2008 [18].

### Secondary outcomes

Secondary outcomes to be assessed when infants are discharged home for the first time are:Survival to discharge home.Microbiologically-confirmed or clinically suspected late-onset invasive infection from trial entry to discharge home.NEC (Bell stage 2 or 3) from trial entry to discharge home.Time taken to reach full milk feeds (tolerating 150 ml/kg/day for 3 consecutive days).Growth (change in z score–weight and head circumference for gestational age) from birth to discharge home.Duration of parenteral feeding.Length of time in intensive care.Length of hospital stay to discharge home.

In addition, the separate components of the composite primary outcome at 24 months of age corrected for prematurity will be analysed individually as secondary outcomes. The diagnosis of cerebral palsy by a doctor or other health professional will also be a secondary outcome assessed at this age.

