### Randomisation and allocation

Randomisation will take place at the time the clinician is ready to start increasing the feed volume. This will be performed through a secure website hosted by the NPEU CTU with telephone back-up available 24/7, 365 days a year.

A minimisation algorithm will be used to ensure balance on important prognostic factors: hospital, multiple birth, gestational age ranges, and birth weight <10th centile for gestational age. Multiple births will be given the same allocation.

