### Sample size and power

The primary comparison will be the difference in the proportion of infants surviving without moderate or severe disability at 24 months of age corrected for prematurity. Based on previous trials, it is estimated that 80% of the infants will survive to 2 years, and that 11% of these will have a moderate or severe disability [19]. Hence it is estimated the proportion surviving without moderate or severe disability in the control group receiving the 18 ml/kg/day increment will be 71%. With a total sample size of 2500 and allowing for a response rate of 80%, there will be 90% power to detect an absolute difference of 6.3% (from 71.0% in the control group to 77.3%) in this proportion, with a two-sided 5% significance level.

With the same level of significance, a sample size of 2500 infants will have 90% power to detect an absolute risk difference of 5.4% (from 25.0% in control group to 19.6%) in the incidence of sepsis [20] and an absolute risk difference of 3.5% (from 6.0% in control group to 9.5%) in the incidence of NEC (Bell stage 2 or 3) [21–23].

An inflation factor of 1.12 was applied to the sample size to allow for multiple births, expected to have correlated outcomes, receiving the same allocation. This was based on an estimate of 25% for the proportion of multiple births and an intraclass correlation coefficient of 0.9 for the primary outcome at 2 years, based on a similar outcome in a preterm population [24]. The total number of babies that will be recruited will be 2800.

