### Statistical analysis

Demographic factors, clinical characteristics and outcomes will be summarised with counts (percentages) for categorical variables, mean (standard deviation) for Normally distributed continuous variables, or median (interquartile or entire range) for other continuous variables. Infants will be analysed according to allocation regardless of the speed of milk feed increase they actually receive.

The two groups will be compared using generalised estimating equations, adjusting for the minimisation factors to account for the correlation between treatment groups. This method of analysis will also account for the correlation in outcomes between twins and siblings born in a subsequent pregnancy during the trial period. For the primary outcome, an adjusted risk ratio with 95% confidence will be calculated using log binomial regression, or log poisson regression with a robust variance estimator if the binomial model fails to converge [25]. Linear regression will be used for Normally distributed outcomes, quantile regression for skewed continuous variables, and Cox regression for time to event outcomes. Ninety-nine percent confidence intervals will be calculated for all secondary outcomes.

The consistency of the effect of advancing milk feeds across specific subgroups of infants will be assessed using the statistical test of interaction. Pre-specified subgroup analyses include: (i) week of gestation at birth, (ii) birth weight (<10th centile for gestational age versus ≥ 10th centile and (iii) type of milk (breast milk only/formula only/mixed). Subgroup analysis will be performed on the primary outcome, and the incidence of sepsis and NEC.

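### Growth is compared as change in z score without the continuous birth z score as a covariate, which gives up some precision, most clearly for head circumference

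*Protocol article*

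**What the plan says.** The Secondary outcomes section of the protocol article lists growth, as the change in z score for weight and "head circumference for gestational age) from birth to discharge home", among eight outcomes assessed at first discharge home. The Abstract also names growth among the secondary outcomes.

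The Statistical analysis section sets a common approach for all outcomes: "The two groups will be compared using generalised estimating equations, adjusting for the minimisation factors". For continuous outcomes it adds: "Linear regression will be used for Normally distributed outcomes, quantile regression for skewed continuous variables". On precision it says: "Ninety-nine percent confidence intervals will be calculated for all secondary outcomes".

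The Randomisation and allocation section gives the factors that enter that adjustment: "hospital, multiple birth, gestational age ranges, and birth weight <10th centile for gestational age".

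Read together, these describe a regression of the change score on allocation and the four minimisation factors. Birth-weight z score enters only as a two-level split at the 10th centile. Birth head circumference is not named in any form.

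**The concern.** A change score subtracts the birth value with a fixed coefficient of 1. If the slope of discharge z score on birth z score is not 1, the leftover dependence on birth z score stays in the residual. It widens the interval, and it lets a fraction of any chance difference between the arms at birth into the estimate. Putting birth z score in the model removes both effects.

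The value needed is already collected, because the change cannot be computed without it. Growth also bears directly on a feeding intervention, and 99% intervals are wide enough that avoidable variance is worth removing.

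The planned covariates do only part of this work. The centile split treats an infant at the 11th centile like one at the 90th. For head circumference it is an indirect proxy. The z scores are already standardised for gestational age, so the gestational-age ranges should add little.

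**Working it through.** **The plan's own figures.** The article gives no sample size or power for growth, so there is nothing to reproduce for this outcome. The primary calculation supplies only the number per arm: "With a total sample size of 2500 and allowing for a response rate of 80"%, that is 1250 per arm, or 1000 with a response. For 71.0% against 77.3% with 1000 per arm, the standard error is √(2 × 0.7415 × 0.2585 / 1000) = 0.01958 under no difference and √((0.71 × 0.29 + 0.773 × 0.227) / 1000) = 0.01953 under the alternative. Power is Φ((0.063 − 1.96 × 0.01958) / 0.01953) = Φ(1.261) = 89.6%, which agrees with the stated 90%. It has no bearing on growth.

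**Assumptions for growth (none is in the article).**
- Birth-discharge correlation r between 0.5 and 0.8.
- Equal SDs at birth and discharge, relaxed below.
- Normal z scores.
- 10 to 30% of infants below the 10th centile.
- 1250 per arm with growth data, ignoring clustering of multiples and deaths before discharge.

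**Formulas.** Let s0 and s1 be the birth and discharge SDs.
- Change score: s0² + s1² − 2r·s0·s1
- Adjusted for birth z: s1²(1 − r²)
- Excess of the first over the second: (s0 − r·s1)², never negative
- Equal SDs: ratio = (1 − r²) / (2(1 − r)) = (1 + r)/2

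For weight the fair comparator is the planned model, which already has the centile term. If a share p lies below the cut at normal quantile c, the term explains R² = φ(c)² / (p(1 − p)) of birth-weight z variance: 0.34, 0.49 and 0.58 for p = 10%, 20% and 30%. In units of SD², the planned variance is (1 − r)²(1 − R²) + (1 − r²).

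**Variance with birth z score, divided by variance without it.**

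| r | Head circumference, no other covariate | Weight, p = 10% | Weight, p = 20% | Weight, p = 30% |
|---|---|---|---|---|
| 0.5 | 0.750 | 0.820 | 0.855 | 0.876 |
| 0.6 | 0.800 | 0.859 | 0.887 | 0.904 |
| 0.7 | 0.850 | 0.896 | 0.917 | 0.930 |
| 0.8 | 0.900 | 0.932 | 0.946 | 0.955 |

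The reduction is 10 to 25% for head circumference and 4.5 to 18% for weight. Interval widths go with the square root: about 5 to 13% narrower for head circumference and 2 to 9% narrower for weight.

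**On the outcome scale.** At r = 0.5 the raw change score has variance 2(1 − 0.5) = 1 and standard error √(2/1250) = 0.040, so the 99% half-width is 2.576 × 0.040 = 0.103 SD. With birth z score the standard error is √(0.75 × 2/1250) = 0.0346 and the half-width 0.089 SD. The difference is 0.014 SD, at the favourable end of the assumed range.

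**Chance imbalance.** One standard error of imbalance in birth z score is √(2/1250) = 0.04 SD. A change score carries over the fraction (1 − r): 0.5 × 0.04 = 0.020 SD at r = 0.5 and 0.2 × 0.04 = 0.008 SD at r = 0.8. For weight, the centile term multiplies this by √(1 − R²), giving about 0.005 to 0.016 SD.

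**Unequal SDs.** Set s0 = 1.
- s1 = 1.2, r = 0.7: adjusted variance 1.44 × 0.51 = 0.734; excess (1 − 0.84)² = 0.026; ratio 0.734/0.760 = 0.97, so almost no gain.
- s1 = 0.9, r = 0.7: adjusted variance 0.81 × 0.51 = 0.413; excess (1 − 0.63)² = 0.137; ratio 0.413/0.550 = 0.75, a larger gain than the 0.85 with equal SDs.

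**The case against.** The strongest reply is that the Statistical analysis section is one condensed paragraph for all outcomes. It has no growth-specific model and does not rule birth z score out. Covariates for one secondary outcome are often left to the SAP, which is not shown. This stands to the extent that the article does not prove the covariate will be left out. It does not remove the point, because the article names the outcome, the model family and the adjustment set, and that stated analysis has a better alternative at no cost.

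The second reply is that weight is already partly handled: the centile factor is balanced by minimisation and then adjusted for. This stands, and it is why the weight gain is measured against the planned model. It does not carry over to head circumference, for which no birth measure is named.

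The third reply is that little depends on the result. Growth is one of eight discharge outcomes, the power statement covers the primary outcome, sepsis and NEC, and the size of the gain rests on correlations and SDs that the article does not give. This also stands, and it limits the weight of the point, though not its direction.

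**Conclusion.** The point holds as one of efficiency. As stated, the growth comparison omits a baseline value that must already be available, and including it would make the estimate at least as precise. Under equal SDs and r of 0.5 to 0.8, the variance reduction is 10 to 25% for head circumference, ignoring other covariates, and about 4.5 to 18% for weight beyond the centile term. It can be close to nil if the discharge SD exceeds the birth SD.

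A reader might infer more than the article supports:
- That growth is analysed with no baseline adjustment. For weight it is adjusted for the centile split.
- That a baseline imbalance passes in full into the effect. A change score has already subtracted baseline, and only the fraction (1 − r) remains, about 0.01 to 0.02 SD per one-standard-error imbalance.
- That regression to the mean biases the comparison. It acts on both randomised arms alike, and the estimate is unbiased over randomisations.
- That the full 10 to 25% applies to weight. That figure uses a raw change score as comparator, which is not the planned analysis for weight.

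This is a minor improvement for one secondary outcome. The primary outcome and the stated power are unchanged.

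**What to change.** Keep growth defined as change in z score and keep the adjustment for the minimisation factors. Add the continuous birth-weight z score to the weight model and the continuous birth head-circumference z score to the head-circumference model. Fix this before the growth data are analysed by arm, or confirm that the SAP already does so.

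The outcome definition need not change. With birth z score in the model, the allocation coefficient is identical to that from modelling discharge z score on birth z score, because subtracting a covariate from the outcome alters only that covariate's own coefficient.

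The cost is one extra covariate in each of two models, with no new data collection and no change to sample size.

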### Trial procedures

#### Informed consent

Written consent will be sought from parents only after they have been given a full verbal explanation and written description of the trial via a parent information leaflet. Consent will be obtained by means of dated parental signature on a study consent form and the signature of the person who obtained informed consent. Recruitment will be conducted by a health professional with delegated authority. Parents who do not speak English will only be approached if an interpreter is available.

### Remuneration

Parents will not be given any financial or material incentive or compensation for enrolling their babies in this trial.

### Randomisation and allocation

Randomisation will take place at the time the clinician is ready to start increasing the feed volume. This will be performed through a secure website hosted by the NPEU CTU with telephone back-up available 24/7, 365 days a year.

A minimisation algorithm will be used to ensure balance on important prognostic factors: hospital, multiple birth, gestational age ranges, and birth weight <10th centile for gestational age. Multiple births will be given the same allocation.

### Blinding

This is an open trial; blinding of the clinicians, nursing staff, and parents is not possible. A blinded endpoint review committee will examine the relevant data collection forms and clinical notes of infants with possible sepsis and NEC and classify them systematically according to predefined criteria.

### Stopping or modifying the trial intervention

Deviations from the scheduled speed of increase may be made at the discretion of the treating clinician if the infant appears unable to tolerate the allocated speed of milk feed increase.

